## Abstract

**Background:**

Hospital treatment of chronic obstructive pulmonary disease (COPD) frequently does not follow published evidences. This lack of adherence can contribute to the high morbidity, mortality and readmissions rates. The European Quality of Care Pathway (EQCP) study on acute exacerbations of COPD (NTC00962468) is undertaken to determine how care pathways (CP) as complex intervention for hospital treatment of COPD affects care variability, adherence to evidence based key interventions and clinical outcomes.

**Methods:**

An international cluster Randomized Controlled Trial (cRCT) will be performed in Belgium, Italy, Ireland and Portugal. Based on the power analysis, a sample of 40 hospital teams and 398 patients will be included in the study. In the control arm of the study, usual care will be provided. The experimental teams will implement a CP as complex intervention which will include three active components: a formative evaluation of the quality and organization of care, a set of evidence based key interventions, and support on the development and implementation of the CP. The main outcome will be six-month readmission rate. As a secondary endpoint a set of clinical outcome and performance indicators (including care process evaluation and team functioning indicators) will be measured in both groups.

**Discussion:**

The EQCP study is the first international cRCT on care pathways. The design of the EQCP project is both a research study and a quality improvement project and will include a realistic evaluation framework including process analysis to further understand why and when CP can really work.

**Trial Registration number:**

NCT00962468

## Background

Healthcare is changing towards more patient focused care. The organization of the care process related to quality, efficiency and accessibility is one of the main areas of interest within the next years for clinicians, healthcare managers and policy makers. A main method to (re)organize a care process is the development and implementation of a care pathway. Care pathways, also known as clinical pathways or critical pathways, are used worldwide for a variety of patient groups [1-7]. A care pathway is defined as a complex intervention for the mutual decision making and organization of predictable care for a well-defined group of patients during a well defined period. Defining characteristics of pathways includes: an explicit statement of the goals and key elements of care based on evidence, best practice and patient expectations; the facilitations of the communication and coordination of roles, and sequencing the activities of the multidisciplinary care team, patients and their relatives; the documentation, monitoring, and evaluation of variances and outcomes; and the identification of relevant resources [4,8,9].

A care pathway is explicitly defined as a "complex intervention" [4,8-11]. Complex interventions in healthcare, whether therapeutic or preventive, comprise a number of interacting components which seem essential to the proper functioning of the intervention although the "active component'' of the intervention that is effective, is difficult to specify. Considering a spectrum of low to high complexity such as developing a drug would be at the low end of complexity spectrum and the evaluation of the effect of a stroke unit would be at the high end of the spectrum. The greater the difficulty in defining precisely what the "active component" of an intervention is, and how they relate to each other, the greater the likelihood that you are dealing with a complex intervention [12-14]. Pathways in the line of stroke units seem to be at the higher end of the complexity spectrum. Active ingredients of a care pathway complex intervention might be the level of multidisciplinary teamwork, the integration of a package of evidence based key interventions and the active follow-up of the care process [6].

A recent Cochrane review concludes that clinical pathways are associated with reduced in-hospital complications and improved documentation without negatively impacting on length of stay and hospital costs [15]. The effects are however still quite small in comparison of what we might expect theoretically. One possible reason is the high variability in effect from one organisation to another organisation what seems to stress that context factors might be extremely important [9,16,17]. These context factors are not taking well in these meta-analyses as context is really stripped off. An indicator of context influence is the heterogeneity of the meta-analysis, which seems to be quite high in the Rotter meta-analysis paper [15]. Large multicenter trials including information on the mechanisms used and the context of the involved organizations will be important to fully understand why and when pathways lead to their effect [9,18].

To evaluate pathway effectiveness the European Pathway Association, an international not for profit association, launched the European Quality of Care Pathways (EQCP)-study on exacerbation of Chronic Obstructive Pulmonary Disease (COPD) [18]. COPD is worldwide a leading cause of acute hospital admission [19]. Patients with COPD exacerbation need multidisciplinary care and the coordination of the care process among multiple caregivers is complex [20]. Thirty five percent of COPD patients are admitted because of acute exacerbation within one year [21]. Up to 40% of admitted patients having two or more readmissions a year [22,23]. A systematic review about in-hospital management of COPD exacerbation showed that implementation of care processes recommended by worldwide accepted guidelines is very poor and show high variance, especially for performance of non pharmacological interventions [24]. Also Decramer et al. (2003) found several important deviations from international guidelines in the management of COPD by pulmonologists and general practitioners [25].

Up to now two non-randomized trials about the impact of a care pathway for inpatient management of COPD exacerbation are published [26,27]. The studies have been conducted between 2000 and 2001, and the methodology was rather weak. However the studies suggest that a COPD exacerbation care pathway improves performance with regard to diagnostic assessment and use of standing orders, and that it may reduce length of stay and the number of hospitalisations.

### Objectives

The primary goal of the EQCP study on COPD is to evaluate the care pathway effectiveness in acute hospitals. A secondary goal is to understand how and under which circumstances the implementation of a pathway for COPD is successful.

## Methods

### The project

The European Quality of Care Pathways (EQCP) study is an international multicentre research project launched the European Pathway Association (E-P-A) http://www.E-P-A.org, an international not for profit association [18]. The E-P-A is collaborating with the Center for Health Services and Nursing Research of the Faculty of Medicine of the Catholic University Leuven (Belgium) and the School of Public Health of the Amedeo Avogadro University of Eastern Piedmont (Italy) for the scientific lead of the this study. The study runs in four countries: Belgium, Ireland, Italy and Portugal. In each country, a research centre is coordinating the project in the own country based on the international agreed protocol. In Belgium the lead coordinating centre is the Center for Health Services and Nursing Research of the Faculty of Medicine of the Catholic University Leuven. For Ireland, the lead centre is the Health Service Executive in Dublin. In Italy, the School of Public Health of the Amedeo Avogadro University of Eastern Piedmont is coordinating the project with support from ARESS Piemonte. In Portugal, the lead coordinating centre is National School of Public Health in Lisbon. In each of the four countries hospitals will be selected by E-P-A in close cooperation with a national coordinator. In every participating hospital a pathway facilitator is appointed as local facilitator for implementing the care pathway. The pathway facilitator is trained by the E-P-A team in implementing care pathways, except for Belgium where hospitals were selected among members of the Belgian-Dutch Clinical Pathway Network and all pathway facilitators were trained before in the network [18].

### Study design

To evaluate the effect of a care pathway, a cluster Randomized Controlled Trial (cRCT) will be used [12-14]. In cRCTs organizations, rather than individuals, are randomized to an intervention and a control group, and outcomes are measured on individual level within the clusters [14]. Each cluster consist of patients hospitalized for a COPD exacerbation in a particular hospital and cared for by a specific multidisciplinary team.

Stratified randomization will be used to assign hospitals to an intervention group (development and implementation of an evidence based care pathway) and a control group (no intervention/usual care). Literature showed that several organizational factors could have significant impact on performance of key interventions and outcomes. To ensure that hospitals in both arms are in balance, hospitals will be stratified on country-level, according to the following variables: hospital type (teaching versus non teaching), hospitals size (< 600 and ≥600 beds) and annual volume of COPD-patients (< 300 and ≥300). Furthermore, the following organizational factors will be explored: availability of an early discharge scheme, presence of local guidelines about follow-up of patients after discharge, presence of a formal pulmonary rehabilitation program, availability of non-invasive ventilation, and annual volume of patients treated for COPD exacerbation. These variables will be treated as covariates in the data analysis. To the hospitals included in the control group will be offered the opportunity to develop a care pathway one year later, based on the protocol and experience gained in the experimental group, in order to increase their participation. By this means the design incorporated some characteristics of a step wedge design in which the implementation of the intervention is spread over time (see figure 1).

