### Study sample

Sample size calculation in a cRCT is based on the improvement in the main outcome parameters [13,14]. The selection of main outcomes for the EQCP-study is based on three criteria: frequency of use in the literature, opinions of experts and timing of the research project with respect to organizational constraints (sustainability of the design, time to include patients). Based on these criteria, six-month readmission rate was identified as the main study outcome for in-hospital management of COPD exacerbation ([24]; [name], [name], [name], [name], [name], [name], [name], [name]. Selection of indicators for research on COPD care pathways: an international Delphi study. submitted). Two other important outcome parameters are 1-year mortality and length of in-hospital stay. Based on a power of 80% and an α of 0.05 (two-sided), 296 patients per arm are needed to observe a 10 percent reduction rate in readmission of 41% to 30% [28,29]. After adjustment for the cluster design, based on two previous cRCT by Panella et al [30,31] (ICC: 0.018; IFF: 1.342; n = 20) the effective sample size increased to 398 patients per arm. This means that, based on a number of 20 consecutive admitted patients in each unit, 20 hospitals should be included both in each intervention and control groups. As four countries are actually involved in the study, every country has to enroll at least ten hospitals that have to be randomized into five cases and five controls [30,31].

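### Three crossed two-level stratifiers within four countries make 32 cells for about 40 hospitals, so stratified randomisation as named guarantees neither factor balance nor the 5:5 split per country

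*Protocol article*

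**What the plan says.** The Study design section names the method: "Stratified randomization will be used to assign hospitals to an intervention group" or to a usual-care control group. It also gives the purpose, the level and the factors: to balance the arms, "hospitals will be stratified on country-level, according to the following variables: hospital type (teaching versus non teaching), hospitals size" (cut at 600 beds) and annual COPD volume (cut at 300), each with two levels. The Project section fixes the number of countries: "The study runs in four countries: Belgium, Ireland, Italy and Portugal". The Study sample section derives 20 hospitals per arm and then adds that "every country has to enroll at least ten hospitals that have to be randomized into five cases and five controls".

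The article does not say whether the three factors are fully crossed, although that is the natural reading. It states no block size, pairing, minimisation or other constraint that would tie the stratification to the 5:5 requirement. After listing some further organisational factors, the Study design section says that these variables will be covariates in the analysis. It is unclear whether that sentence also covers the stratifiers.

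**The concern.** Stratification protects balance when each stratum holds enough units for the within-stratum blocks to fill. Here the units are hospitals, about ten per country, spread over eight possible cells. Many cells will hold one hospital or an odd number, and the unpaired hospital in each such cell is in effect allocated by a coin toss. These tosses are independent across cells, so nothing brings the country total back to five and five, and nothing balances the factors across the leftover hospitals.

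The article's own rationale is that organisational factors could matter for care performance and outcomes. With 20 clusters per arm, a difference of a few hospitals on teaching status, size or volume would be visible in the baseline table and would cost precision. The stated aim, "To ensure that hospitals in both arms are in balance", promises more than the named method provides at this number of clusters.

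**Working it through.** **Inputs from the article.** Four countries (The project); three two-level factors (Study design); 41% versus 30%, two-sided alpha 0.05, power 80%, ICC 0.018, cluster size 20, at least ten hospitals per country split 5:5 (Study sample).

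**The plan's own figures.** The two-proportion formula with pooled variance and no continuity correction gives 296 per arm, as stated. The design effect is 1 + (20 - 1) x 0.018 = 1.342. Then 296 x 1.342 = 397.2, rounded up to 398 per arm, and 398 / 20 = 19.9, so 20 hospitals per arm and 40 in total. These figures reproduce.

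**Cells.** 4 x 2 x 2 x 2 = 32, and 40 / 32 = 1.25 hospitals per cell. Within a country there are 8 cells for 10 hospitals.

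**Assumptions.** Full crossing; exactly ten hospitals per country; an independent permuted-block list in each cell. The article gives no prevalences, so the factors were set at 50/50/50% or 30/30/40%, either independent or correlated (correlation 0.6 on an underlying normal scale). Each range below spans these settings.

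**Sparseness.** About 19-24 of the 32 cells are occupied across the trial, and about 10-12 hold a single hospital. Per country, about 4.7-5.9 cells are occupied and 3.2-3.8 hospitals are left unpaired under blocks of 2.

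**The 5:5 split, checked by hand.** With blocks of 2, a country with m odd-sized cells has m independent coin tosses, and m is even because ten is even. So P(5:5) = C(m, m/2) / 2^m:
- m = 2: 2/4 = 0.50
- m = 4: 6/16 = 0.375
- m = 6: 20/64 = 0.31

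With 3.2-3.8 unpaired hospitals on average, the answer must lie near 0.4, which agrees with the simulation:

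| Within-cell blocks | 5:5 in a given country | 5:5 in all four | 20:20 overall | Mean total arm difference (hospitals) |
|---|---|---|---|---|
| of 2 | about 40-45% | about 3-4% | about 21% | about 3 |
| of 4 | 31-36% | about 1% | 15-18% | 3.5-4.1 |

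**Factor balance.** Probability that at least one of the three factors differs between arms by 2 or more hospitals within a country:

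| Allocation | Probability |
|---|---|
| Simple randomisation | 71-84% |
| Unstratified 5:5 within country | 62-72% |
| Blocks of 2 in each crossed cell | 46-57% |
| Paired within cells, leftovers split evenly to 5:5 | 27-38% |
| Random draw from the best-balanced 50 of the C(10,5) = 252 allocations | 3-8% |

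Over the whole trial, the mean absolute arm difference per factor is 2.0-2.2 hospitals with blocks of 2 and 2.4-2.9 with blocks of 4. It is 2.4-2.5 with an unstratified 5:5 block per country and 1.5-1.6 with the paired 5:5 scheme.

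**Power cost of unequal arms.** The effective number per arm is 2 x n1 x n2 / (n1 + n2). For 18:22 this is 2 x 18 x 22 / 40 = 19.8, and for 16:24 it is 2 x 16 x 24 / 40 = 19.2, against 20. The loss is small.

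**The case against.** The strongest reply is that the article never states independent lists per crossed cell, so every failure probability rests on an assumed mechanism. Read together, the Study design and Study sample sections could describe one coherent scheme: 5:5 within each country, balanced on the three factors. Pairing within cells and splitting the leftovers evenly meets 5:5 in every run. A condensed article may also leave allocation mechanics to the full protocol.

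Much of this stands, and it rules out several stronger readings that a reader might infer.
- The plan has not been shown to be unable to deliver balance or 5:5. The shortfall depends on full crossing and independent allocation within cells, neither of which is stated, and ten hospitals per country is a minimum.
- The scheme is not close to simple randomisation: 46-57% against 71-84% on the same measure. Only with blocks of 4 does the advantage over an unstratified 5:5 block disappear.
- Chance imbalance under random allocation does not bias the estimator. It adds variance, and adjustment can recover part of that.
- Some adjustment is already planned, since the covariate list includes the annual volume of patients treated for COPD exacerbation.
- The article gives no basis for supposing that anyone would force 5:5 by hand.

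The reply does not remove the point. Independent allocation within strata is the ordinary meaning of the method the article names, and at 1.25 hospitals per cell that method does not secure the stated aim. If a constrained or paired scheme is intended, the term used does not describe it.

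**Conclusion.** The point holds in a limited form. On the natural reading there are 32 cells for about 40 hospitals. Ordinary within-cell allocation then improves on simple randomisation, but it guarantees neither factor balance nor the required split. With blocks of 2, 5:5 is reached in about 40-45% of countries and in all four about 3-4% of the time, and a factor is off by 2 or more hospitals in about half of countries (46-57%).

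These figures rest on assumed block size, prevalences, full crossing and ten hospitals per country. The consequence is chance covariate imbalance and some loss of precision, with little power lost through unequal arms; no effect on the readmission estimate itself has been quantified. It is more than a missing detail, because the named method falls short of its stated aim and a clearly better one is available at low cost.

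**What to change.** Replace crossed-cell stratification with covariate-constrained randomisation within country. Once a country's hospitals are signed up, list all 5:5 allocations (252 for ten hospitals) and score each on teaching status, beds and COPD volume, using continuous values for the last two where available. Then draw one at random from a pre-specified best-balanced set, for example the best 20%. This always gives 5:5 and brings the imbalance measure to about 3-8%.

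If hospitals must be randomised sequentially, use minimisation with a random element within country. Minimisation does not by itself guarantee an exact 5:5, so the article should then say how the split is reached.

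In either case, state plainly that country and the three balancing factors are in the analysis model.

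The cost is a short program and a few sentences, settled before any hospital is randomised. The one practical downside is that a country's hospitals must be recruited before they are randomised together.

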**Figure 1 F1:**
[figure not shown]
**The EQCP study design**.

### Inclusion - exclusion criteria

Organizations will be included if they will provide written agreement to participate and agree that they will not develop and implement a pathway for COPD within the time frame of the study when randomized in the control group. All consecutive patients admitted for COPD exacerbation will be included in the study if (i) they will provide written informed consent; (ii) they will be hospitalized for at least 48 hours, (iii) they will be admitted on the ward where the COPD exacerbation is usually treated (respiratory ward, geriatric ward, general medicine ward) and (iv) if they will be able to understand and read the native language. Each patient will be included only once in the study at initial admission, even if the patient will be hospitalized more than once during the study period. Patients will be excluded from the study if they will require invasive positive pressure ventilation, or if they are already included in another study of which the measurements could influence the measurements or outcomes of the EQCP-study.

### Study sample

Sample size calculation in a cRCT is based on the improvement in the main outcome parameters [13,14]. The selection of main outcomes for the EQCP-study is based on three criteria: frequency of use in the literature, opinions of experts and timing of the research project with respect to organizational constraints (sustainability of the design, time to include patients). Based on these criteria, six-month readmission rate was identified as the main study outcome for in-hospital management of COPD exacerbation ([24]; [name], [name], [name], [name], [name], [name], [name], [name]. Selection of indicators for research on COPD care pathways: an international Delphi study. submitted). Two other important outcome parameters are 1-year mortality and length of in-hospital stay. Based on a power of 80% and an α of 0.05 (two-sided), 296 patients per arm are needed to observe a 10 percent reduction rate in readmission of 41% to 30% [28,29]. After adjustment for the cluster design, based on two previous cRCT by Panella et al [30,31] (ICC: 0.018; IFF: 1.342; n = 20) the effective sample size increased to 398 patients per arm. This means that, based on a number of 20 consecutive admitted patients in each unit, 20 hospitals should be included both in each intervention and control groups. As four countries are actually involved in the study, every country has to enroll at least ten hospitals that have to be randomized into five cases and five controls [30,31].

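### The sample size makes no allowance for having only 40 hospitals: 20 per arm give about 78% power at a true two-sided 5% level, not the stated 80%

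*Protocol article*

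**What the plan says.** All the figures are in the Study sample section of the protocol article. The starting point is "Based on a power of 80% and an α of 0.05 (two-sided), 296 patients per arm are needed", for assumed six-month readmission proportions of 41% under usual care and 30% with the pathway. The clustering inputs are given as "ICC: 0.018; IFF: 1.342; n = 20", after which "the effective sample size increased to 398 patients per arm". With 20 patients per hospital, the section concludes that "20 hospitals should be included both in each intervention and control groups". Recruitment is then set by country: "every country has to enroll at least ten hospitals that have to be randomized into five cases and five controls".

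The Study design section makes the hospital the unit of allocation ("In cRCTs organizations, rather than individuals, are randomized to an intervention and a control group"). It stratifies by hospital type, size and COPD volume within country and lists further organisational factors, of which it says "These variables will be treated as covariates in the data analysis". The article does not name the test for the primary outcome, and the sample-size text mentions no adjustment for the number of hospitals.

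**The concern.** The 1.342 factor and the number of hospitals address two different things. The factor says how much larger the variance of an arm's readmission proportion is because patients within a hospital resemble each other. The number of hospitals determines how well that variance can be estimated. With 20 hospitals per arm the test statistic follows, approximately, a t distribution on 38 degrees of freedom, with a two-sided 5% critical value of 2.024 rather than 1.960. A calculation based on 1.960 treats the between-hospital variance as known.

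What is at stake is whether the 80% power and the two-sided 5% level printed together in the article are both delivered by 20 hospitals per arm. Rounding up to whole hospitals leaves almost no slack, so even a small omission takes the design below its target.

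**Working it through.** **Inputs.** From the Study sample section: 41% v 30%, two-sided α 0.05, power 80%, ICC 0.018, 20 patients per hospital, 20 hospitals per arm. Assumptions added here: equal hospital sizes, the ICC taken as known for planning, complete outcome data, and no covariates in the base case.

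**1. Reproduce the plan.**
- Mean proportion: (0.41 + 0.30)/2 = 0.355.
- n per arm = [1.960 × √(2 × 0.355 × 0.645) + 0.842 × √(0.41 × 0.59 + 0.30 × 0.70)]² / 0.11² = 295.9, so 296.
- Design effect: 1 + (20 − 1) × 0.018 = 1.342.
- 296 × 1.342 = 397.2, so 398.
- 398/20 = 19.9, so 20 hospitals per arm, or 400 patients.

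Other versions do not fit: 314 with continuity correction, 233 one-sided, 361 for 41% v 31%. The normal-quantile formula accounts for the whole chain, so no small-sample correction is hidden in it. With 400 per arm the plan's formula gives 80.3% power.

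**2. Standard error of the difference for 20 × 20 per arm.** The effective number per arm is 400/1.342 = 298.1.
- Unpooled: √[(0.2419 + 0.2100)/298.1] = 0.0389, so the noncentrality is 0.11/0.0389 = 2.825.
- Pooled: √[2 × 0.355 × 0.645/298.1] = 0.0392, so the noncentrality is 0.11/0.0392 = 2.806.

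**3. Power, comparing like with like.** The noncentral t has 2 × (20 − 1) = 38 degrees of freedom and critical value 2.024.

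| Variance | Normal, 1.960 | t, 38 df | Loss |
|---|---|---|---|
| Unpooled | 80.7% | 78.6% | about 2.0 points |
| Pooled | 80.1% | 78.1% | about 2.1 points |

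The plan's 80.3% mixes the two variances (pooled under the null, unpooled under the alternative), so it should not be set directly against either t figure. Against the 80% target the shortfall is 1.4 to 1.9 points.

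**4. Type I error if 1.96 were used.** P(|t| > 1.96) on 38 degrees of freedom is 5.7%.

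**5. Simulation check.** Beta-binomial data were generated for 20 hospitals of 20 per arm with ICC 0.018 and analysed with a t-test on hospital proportions (200,000 runs per scenario).
- With the t critical value: power 78.5%, type I error 5.0%.
- With 1.96: power 80.2%, type I error 5.75%.

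**6. Hospitals needed for 80%.** With 21 per arm (420 patients, 40 degrees of freedom) power is 80.6% unpooled or 80.1% pooled. That is 5% above the planned 400 (420/400 = 1.05).

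**The case against.** **This is a standard approximation.** Nothing in the chain is miscalculated. Normal quantiles multiplied by a design effect are a common planning method, and 296, 1.342 and 398 all stand as outputs of it. This is fair. The error is not in the arithmetic but in presenting the result as 80% power at a two-sided 5% level.

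**The analysis is not shown.** The primary test may well be specified elsewhere, and its absence from a journal article is no fault. A reader might infer that the trial will run with an inflated false-positive rate. The article does not support that, because nothing in it says the analysis will use 1.96. The power statement does not depend on what is unseen: a hospital-level t reference keeps 5% and gives about 78%, while 1.96 recovers about 80% and gives up the 5%.

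**The size is within the uncertainty of the inputs.** On the unpooled t calculation, an ICC of 0.0155 instead of 0.018 gives 80.0%, an ICC of 0.025 gives 74.7%, and 41% v 29.8% gives 80.1%. So the shortfall matters less than the choice of ICC. This stands, and it limits the weight of the point. It does not make 80% the right answer for the inputs printed.

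**Covariates.** One might count country, the three stratifiers and the five organisational factors against the degrees of freedom, reach 32 or 27, and quote power nearer 77%. The article gives no model from which to fix such a count, and that reckoning ignores any precision the covariates gain. Under the stated ICC, between-hospital variation is 20 × 0.018/1.342 = 27% of the variance of a hospital's proportion. On 38 degrees of freedom, cutting the total variance by about 4% (unpooled) to 5% (pooled) would restore 80%. The net effect of covariates could go either way, so the lower figures are not established.

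**Forty hospitals is a minimum.** The country rule says at least ten each, so more may join. That would help, but the power claim is attached to 20 per arm.

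**Conclusion.** The point holds in a limited form. On the plan's own inputs, 20 hospitals of 20 patients per arm give about 78 to 79% power at a true two-sided 5% level (78.6% unpooled, 78.1% pooled), not 80%. The cause is the use of normal quantiles with only 38 hospital-level degrees of freedom. The loss is about two points, before any loss to follow-up, and is minor.

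The conclusion rests on equal hospital sizes, an ICC of 0.018, complete data and an analysis that respects the hospital as the unit of randomisation. A reader might go further and call the trial seriously underpowered. A two-point shortfall that one more hospital per arm would remove does not support that.

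**What to change.** Keep 20 hospitals per arm. In the Study sample section, restate the power as about 78% at a two-sided 5% level, and give the basis: t distribution on hospital-level degrees of freedom, ICC 0.018, 20 patients per hospital, complete data. In the analysis, base the primary test and confidence interval on hospital-level (small-sample) degrees of freedom, which protects the 5% level.

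The cost is one sentence in the sample-size section and one line in the analysis, with no added hospitals or patients. The stated power becomes slightly less favourable, and the interval is about 3% wider than with 1.96 (2.024/1.960 = 1.033). Adding hospitals to recover 80% is not needed for so small a gap. Under an equal split within each of four countries the next step is 24 per arm, since 21 cannot be divided evenly.
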